### **Data Access/Sharing.**

As described above, all data collected via cell phone and web-based questionnaires will be stored by Talaria on secure servers. Clinical data collected at MRN/UNM will be stored at MRN in the lab of [name]. All clinical data will be kept in research folders in a locked file cabinet, identified only by URSI number. For the purposes of data analyses at the end of the study, [name] will send a password-protected electronic data file to [name], containing coded clinical data (e.g., diagnostic data, side effects, etc.) which will be labeled only by URSI number. Data from the two sites will be merged by [name] and sent back to [name] so both investigators can assist with data analyses.

Additionally, consistent with other studies in [name] lab, we will seek participants' permission for data sharing in the event they participate in more than one study in our lab or at MRN. MRN has a standardized data sharing procedure based on URSI number). Participants will respond to a separate box on the consent form to indicate whether they agree to data sharing.

---

iii) Describe methods by which data will be analyzed and interpreted. Include the following, if applicable:

Data will be analyzed using traditional General Linear Model analyses, e.g., a mixed-groups ANOVA to evaluate main effects intervention condition (AGATE vs. SASSED) pm adherence over the course of the study.

---

iv) Specific description of any experimental drug, device, or procedure. Any substance or instrument to be used in or on humans which has not received FDA approval for the proposed use requires an IND, IDE, or approval of the Radioactive Drug Research Committee.

N/A

- v) Specific description of any use of biological samples. This is to include their origin, links to identifying information, storage, access, and future use.

Participants will provide a saliva sample for analysis of a genetic variant in the mu opioid receptor gene (OPRM1 A118G, rs1799971), which is demonstrated to influence response to naltrexone (Anton et al., 2008; Ray & [name], 2007). Saliva will be collected in a plastic tube, labeled with the URSI number, and stored in a secure freezer in the neurogenetics lab at MRN. Samples will remain there until they are destroyed (10 years following study completion). Genetic analyses will be conducted in the neurogenetics lab at MRN. OPRM1 will be evaluated as a predictor of response to naltrexone in secondary analyses.

All participants will receive a statement summarizing The Genetic Information Nondiscrimination Act (GINA), which provides protection from risks of future discrimination based on genetic markers. All genetic material will be stored only with unique identifiers in the PI's laboratory. Participants will be informed in writing upon initial consent of the potential risks of genetic research. Consistent with our current protocols, the DNA sample will be kept for a period of 10 years at which time it will be destroyed. In the event that other single genetic markers (single nucleotide polymorphisms, or SNPs) are linked to response to naltrexone are identified, this will allow for analysis of those markers in the future. However, the planned analyses are presently limited to one genetic marker (OPRM1 A118G).

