### III. Hypothesis or Study Goals (questions hoped to be answered by study):

The overall goal of the study is to evaluate the efficacy of a new smartphone-based technology for tracking and enhancing medication adherence. The technology, AGATE (Adaptive Goal-Directed Adherence Tracking and Enhancement), was recently developed by our colleagues at Talaria, Inc. (Seattle, WA) for the purpose of enhancing medication adherence for individuals with alcohol problems. In the current study we will test the efficacy of AGATE for increasing medication adherence in an eight-week pharmacotherapy study of naltrexone. Participants will be randomly assigned to smartphone-based adherence support (AGATE) or a control condition (smartphone alcohol and side effects diary, SASED). A secondary goal is to examine medication effects on patterns of daily drinking using ecological assessments permitted by cell-phone assessments.

The specific hypotheses are as follows:

**Hypothesis 1:** Those assigned to the AGATE condition will be more likely to be classified as adherent to naltrexone (e.g., taking 80% or more of scheduled doses) over the course of the study compared to those assigned to SASED.

**Hypothesis 2:** Those in the AGATE condition will take significantly more scheduled doses compared to those in SASED.

**Hypothesis 3:** Those in the AGATE condition will show better drinking outcomes (defined as higher percentage of days abstinent, lower percentage of heavy drinking days, fewer drinks per drinking day, and longer latency to first heavy drinking day) compared to SASED.

**Hypothesis 4:** Those in the AGATE condition will report higher satisfaction with treatment compared to SASED.

**Hypothesis 5:** Medication adherence will moderate the effect of naltrexone on drinking outcomes, such that the effects of naltrexone on reduced heavy drinking will be increased among those with higher rates of adherence.

**Hypothesis 6:** Adherence outcomes will mediate the effects of condition assignment (AGATE vs. SASED) on drinking outcomes.

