#### Overview of Naltrexone Trial

The purpose of the study is to evaluate whether AGATE effectively measures and enhances medication adherence in the context of a naltrexone trial involving heavy drinkers. Participants will be heavy drinkers recruited from the greater Albuquerque area who are interested in either reducing or stopping their drinking and deemed to be candidates for naltrexone pharmacotherapy by the study physician, [name]. Those enrolled in the study will be prescribed naltrexone (at FDA-approved dose of 50mg once daily) for eight weeks. All participants will receive smartphones during the study. Participants will be randomly assigned to receive either AGATE (adherence support) or SASED, a web-based alcohol and side-effects diary via smartphone. The primary outcome will be percent of scheduled doses that were taken during the eight week trial, as measured by the Medication Event Monitoring System (MEMS, Aardex Group, Union City, CA), pill counts, and the timeline follow-back (TLFB) method. The secondary outcomes will be selected indicators of alcohol use over the 8-week trial.

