6. Female participants of child-bearing age must report use of a birth control method deemed adequate by the study physician, must agree to continue this method over the course of the study, and must agree to contact the study physician if pregnancy is suspected during the study.
- 7.

Note: Because naltrexone is efficacious for reducing heavy drinking in non-dependent individuals (Kranzler et al., 2003), a diagnosis of alcohol dependence is not mandatory for inclusion in the study.

ii) Provide approximate number of subjects (both control and intervention groups).

Our goal is to randomize 105 participants. We anticipate this will leave us with 88 participants at study endpoint after accounting for attrition. Based on our previous experience with medication trials conducted at UNM/MRN, we anticipate conducting phone screenings for approximately 300 participants, of which approximately 140 will qualify to proceed to the in-person screening visit. Our liberal estimate is that 25% of these will be screened out for medical contraindications at the medical assessment before 105 are randomized.

iii) What characteristics (exclusion criteria) would exclude subjects, who are otherwise eligible, from this study? (Answer for each subject group, if different.)

Exclusion criteria will consist of the following:

1. Clinically significant physical illness (based on [name] medical evaluation).
2. Pregnancy or intended pregnancy among female participants.
3. Current (30-day) drug use other than alcohol, nicotine or cannabis (as verified by urine toxicology screen).
4. Any recent (90 day) use of opiate drugs or medications
5. Lifetime opioid dependence as assessed by a structured interview.
6. Currently taking any psychiatric medication other than antidepressants.
7. Lifetime diagnosis of a DSM-IV Axis I psychotic disorder.
8. CIWA score of 8 or higher, indicating clinically significant alcohol withdrawal, at baseline
9. Liver enzyme levels greater than 3x the upper limit of the normal range
10. Currently receiving another pharmacological or behavioral alcohol treatment, with the exception of Alcoholics Anonymous.
11. Currently court-mandated to seek treatment for alcohol problems, or otherwise required to document treatment for alcohol problems.

iv) Please see [HRRC Recruitment Guidelines Section 11.2](#) for more information about acceptable recruitment methods. Describe recruitment (source, initial contact method, etc.)

Described under i) above.

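### The general linear model named for all analyses does not fit the censored time to first heavy drinking day, and its example ANOVA, in classical form, would exclude incomplete adherence records

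*Protocol*

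**What the plan says.** The answer to how data will be analysed (protocol section V.iii, under the Data Access/Sharing heading) is one sentence: "Data will be analyzed using traditional General Linear Model analyses, e.g., a mixed-groups ANOVA" for the effect of condition on adherence over the study. The general linear model family is stated without qualification; only the ANOVA is introduced as an example. Elsewhere the protocol mentions OPRM1 as a predictor in secondary analyses, without a method.

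The outcomes this sentence has to serve are of different types:

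- Section V, Overview of Naltrexone Trial: "The primary outcome will be percent of scheduled doses that were taken during the eight week trial", a continuous percentage.
- Section III, Hypothesis 1: AGATE participants "will be more likely to be classified as adherent to naltrexone", a yes/no outcome with 80% of doses as the example threshold.
- Section III, Hypothesis 3: four drinking measures, one of which is "longer latency to first heavy drinking day".

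Section VI.ii aims to randomise 105 and adds: "We anticipate this will leave us with 88 participants at study endpoint after accounting for attrition". Section VI.vi(3) lets the investigators remove participants who stop the medication of their own accord or repeatedly fail to answer prompts.

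**The concern.** A latency over a fixed 8-week window is censored. Those who never drink heavily in that window, who include the best outcomes, have no value to enter, and neither do those lost before their first heavy drinking day. A linear model has no way to record that a latency exceeds a given number of days. Dropping these people discards much of the contrast between arms; entering their last observed day as if it were an event distorts the estimate.

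The second issue concerns adherence. A classical mixed-groups ANOVA with time as a within-person factor needs every repeated value from each person. If it is run that way on 4-week periods, anyone missing a period leaves the analysis, including any week-4 data already downloaded. Because participants who stop medication may be removed, those excluded may be the less adherent.

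**Working it through.** **Head-counts.** The protocol's figures agree with each other: 140 × (1 − 0.25) = 105 randomised, and 88 / (1 − 0.16) = 104.8, rounded up to 105. Expected loss is 105 − 88 = 17, or 17/105 = 16.2%.

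**Latency: power.** From the protocol: 56 days of follow-up and 105 randomised. Assumed: 1:1 allocation (52 per arm), exponential latency, two-sided 5% level, no dropout. With a proportion p of controls having an event by day 56, the control hazard is −ln(1 − p)/56 and the AGATE event proportion is 1 − (1 − p)^HR; for example, 1 − 0.30^0.6 = 0.514. The protocol gives no event rate, so a range is shown (6,000 simulated trials per row; power in %).

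| Control event rate | HR | AGATE event rate | Linear model, non-events dropped | Linear model, non-events set to day 56 | Log-rank |
|---|---|---|---|---|---|
| 50% | 0.6 | 34% | 5.9 | 32.6 | 38.9 |
| 50% | 0.5 | 29% | 6.2 | 49.4 | 58.5 |
| 70% | 0.6 | 51% | 7.8 | 46.1 | 52.9 |
| 70% | 0.5 | 45% | 10.6 | 70.0 | 76.6 |
| 90% | 0.6 | 75% | 20.5 | 61.8 | 66.7 |
| 90% | 0.5 | 68% | 28.5 | 85.1 | 87.9 |
| 95% | 0.6 | 83% | 31.8 | 66.6 | 69.8 |
| 95% | 0.5 | 78% | 44.5 | 89.0 | 90.6 |

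At HR 1 all three methods reject in 4.3-6.1% of trials. Against log-rank, dropping non-events loses 33 to 66 points; setting them to day 56 loses about 2 to 9.

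**Latency: estimate.** A second simulation (3,000 trials, 52 per arm) let 17/105 of each arm drop out at a uniformly distributed time.

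- Assumed means 20 and 40 days (about 20% censored): true difference 20 days. The linear model shows 10.3 days if censored times count as events and 5.1 if those cases are dropped.
- Assumed means 40 and 80 days (about 41% censored): true difference 40 days. The linear model shows 9.1 and 3.0.

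The fairer target within 56 days is the restricted mean, m(1 − exp(−56/m)). It differs by 30.14 − 18.78 = 11.4 days in the first case and 40.27 − 30.14 = 10.1 in the second. Counting censored times as events therefore falls about one day short of that target and far short of the full mean difference. Dropping the cases recovers less than half of either.

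**Incomplete adherence records.** If all 17 are excluded and would otherwise have given full information, standard errors grow by sqrt(105/88) = 1.092, that is 9.2%. As an illustration, take the MEMS SD of 0.17 from the earlier naltrexone adherence study described in section IV and an assumed difference of 0.10:

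- 44 per arm: 0.10 / (0.17 × sqrt(2/44)) − 1.96 = 0.80, power 78.8%.
- 52.5 per arm: 0.10 / (0.17 × sqrt(2/52.5)) − 1.96 = 1.05, power 85.4%.

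**Hypothesis 1.** Simulated two-arm comparison of a 0/1 outcome, 44 per arm, 40,000 runs. With true rates of 0.5 to 0.9, type I error is 4.3-5.8% for the linear model and 4.5-5.8% for chi-square. Power for 0.60 against 0.85 is 77.1% with both.

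**The case against.** Several stronger readings are tempting, and the protocol does not support them.

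- **A linear model cannot test Hypothesis 1.** A two-arm linear model on 0/1 data gives almost the same test as chi-square. What remains is a mismatch: the example ANOVA addresses adherence over time rather than the 80% classification, and it yields no odds or risk ratio.
- **The plan deletes the 17 dropouts.** No sentence says so. The ANOVA is an example, 88 is expected attrition and not a declared analysis set, and the primary outcome as defined could be one percentage per person, for which deletion across periods does not arise. The exclusion is conditional on the classical repeated-measures form.
- **Standard errors will be 9.2% larger.** That is an upper bound. Section V (Procedures) has MEMS data downloaded when the participant returns, so someone lost before week 4 gives no MEMS record to any model, and someone lost later gives about half.
- **The latency comparison loses most of its power.** This holds for most of the table only if non-events are dropped, which the protocol does not say. With non-events set to day 56 the loss is small. Entrants are regular heavy drinkers, so a high event rate and a loss at the lower end are plausible.
- **The other drinking outcomes need count models.** Nothing in the protocol shows a defect there; two of the four measures are percentages of days.

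It is also fair that drinking outcomes are secondary and that an SAP may add models. The point rests on the method family the protocol does fix for all data, which has no treatment of censoring. That part stands.

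**Conclusion.** The point holds for latency. Followed as written, the plan forces a choice between dropping non-events (about 6-45% power against 39-91% for log-rank) and entering censored times as events (about 2-9 points of power lost and an understated mean difference). These figures rest on assumed event rates, hazard ratios, exponential latency and 1:1 allocation; log-rank was ahead in every non-null case tested.

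For adherence the point is conditional. If the example ANOVA is run classically on repeated periods, up to 17 of 105 are excluded, standard errors are up to 9.2% larger, and selection bias is possible because removal can follow stopping medication. For Hypothesis 1 the issue is effect measure, not validity. The change is worth making, but the protocol does not invalidate its primary comparison.

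**What to change.** Replace the analysis sentence in section V.iii so that each outcome type has a suitable model:

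- **Latency:** Cox regression or a log-rank test, censored at day 56 or at the last drinking report if earlier. The daily smartphone drinking reports supply both dates.
- **Percent of doses taken:** a likelihood-based mixed model using all available records of every randomised participant. State that those who never return after baseline have no MEMS download, and that the model does not by itself remove bias if dropout depends on unrecorded adherence.
- **Hypothesis 1:** logistic regression on the adherent/non-adherent classification.

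This needs no new visits, measures or participants. The cost is slightly more analysis work.

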#### VI. Human Subjects:

- i) Describe characteristics (inclusion criteria) of subject population, including precautions to be taken with vulnerable populations (e.g. children, prisoners, mentally ill/disabled person). Answer for each subject group, if different.

**Participants and Recruitment.** Participants will be heavy drinkers, (ages 21-55) with average weekly consumption  $\geq 14$  standard drinks for women and  $\geq 21$  standard drinks for men over the past 3 months (see below for full inclusion/exclusion criteria). Participants will be recruited primarily using posters/fliers, radio announcements, and newspaper advertisements, using procedures identical to a recently completed pharmacotherapy study for alcohol dependence conducted by [name], who is a co-Investigator in this proposal (HRRC# 07-228). In addition, we may recruit participants who have participated in other studies in the [name] lab, provided that they a) gave consent to be contacted about future studies, b) indicated at the time of participation that they were seeking treatment for alcohol problems or wanted to reduce their drinking (most of [name] studies assess whether the participant is treatment-seeking), and c) meet all other eligibility criteria. Such participants will be identified using existing records and contacted by phone to assess interest in the study. We will not attempt to recruit participants who have taken medication as part of another study in [name] lab. Participants who were screened for a recent study on olanzapine for alcohol dependence (HRRC# 07-228) and did not qualify based on reasons specific to olanzapine may be contacted and assessed for eligibility for treatment with naltrexone in this study.

Eligible participants must meet the following inclusion criteria:

1. Age 21-55
2. Report an average weekly consumption of  $\geq 14$  standard drinks for women and  $\geq 21$  standard drinks for men over the past 3 months (Anton et al., 2006).
3. Report at least two heavy drinking days (defined as 4+ drinks for women and 5+ drinks for men) in a consecutive 30-day period within the 90 days prior to baseline evaluation (Anton et al., 2006).
4. Participants must endorse a desire to reduce or stop drinking alcohol and willingness to try naltrexone.

5. Participants must receive medical clearance by the study physician to take naltrexone (based on blood panels and a medical evaluation).
6. Female participants of child-bearing age must report use of a birth control method deemed adequate by the study physician, must agree to continue this method over the course of the study, and must agree to contact the study physician if pregnancy is suspected during the study.
- 7.

Note: Because naltrexone is efficacious for reducing heavy drinking in non-dependent individuals (Kranzler et al., 2003), a diagnosis of alcohol dependence is not mandatory for inclusion in the study.

ii) Provide approximate number of subjects (both control and intervention groups).

Our goal is to randomize 105 participants. We anticipate this will leave us with 88 participants at study endpoint after accounting for attrition. Based on our previous experience with medication trials conducted at UNM/MRN, we anticipate conducting phone screenings for approximately 300 participants, of which approximately 140 will qualify to proceed to the in-person screening visit. Our liberal estimate is that 25% of these will be screened out for medical contraindications at the medical assessment before 105 are randomized.

iii) What characteristics (exclusion criteria) would exclude subjects, who are otherwise eligible, from this study? (Answer for each subject group, if different.)

Exclusion criteria will consist of the following:

1. Clinically significant physical illness (based on [name] medical evaluation).
2. Pregnancy or intended pregnancy among female participants.
3. Current (30-day) drug use other than alcohol, nicotine or cannabis (as verified by urine toxicology screen).
4. Any recent (90 day) use of opiate drugs or medications
5. Lifetime opioid dependence as assessed by a structured interview.
6. Currently taking any psychiatric medication other than antidepressants.
7. Lifetime diagnosis of a DSM-IV Axis I psychotic disorder.
8. CIWA score of 8 or higher, indicating clinically significant alcohol withdrawal, at baseline
9. Liver enzyme levels greater than 3x the upper limit of the normal range
10. Currently receiving another pharmacological or behavioral alcohol treatment, with the exception of Alcoholics Anonymous.
11. Currently court-mandated to seek treatment for alcohol problems, or otherwise required to document treatment for alcohol problems.

iv) Please see [HRRC Recruitment Guidelines Section 11.2](#) for more information about acceptable recruitment methods. Describe recruitment (source, initial contact method, etc.)

Described under i) above.

v) Describe Informed Consent procedures, including parental/guardian permission and minor assent for studies involving minors. Address any additional measures to be taken with any vulnerable populations. If you are requesting a waiver of informed consent, indicate request and justifications.

- Pre-enrollment: Participant completes phone screen.
- Screening visit: Research assistant provides participant with an overview of the study and provides the

consent form; participant provides informed consent by signing the consent form if they choose. Participant provides blood/urine samples.

- Week 0: Participant completes baseline medical evaluation. If all inclusion criteria and no exclusion criteria are fulfilled to that point, participant receives prescription and is issued a study smartphone.
- Weeks 4 and 8: Return visits for medical interview; blood draw; questionnaires.
- Weeks 0-8: Participant completes daily measures of drinking/adherence; those assigned to AGATE receive medication reminders.

For all recruitment and screening contacts emphasis will be placed on the voluntary nature of the study. Participants will be provided with as much time as they wish to read the consent form and decide upon participation. The ability for participants to withdraw without penalty anytime over the course of the study will be emphasized.

The payments are consistent with ongoing studies in [name] lab, and are not large enough so as to be coercive. Although participants will be allowed to keep their cell phone following the study, we will minimize undue influence by informing them of this after enrollment, not during recruitment.

A trained research assistant will communicate with the participant over the phone and at the screening session. If there is any evidence that the participant does not understand certain information, efforts will be taken to carefully explain that information in more detail. If difficulties persist, the research assistant will notify the PI prior to allowing the participant to provide consent. The PI may decide against enrolling the participant if there is a persistent problem in successfully communicating information related to the study to a particular participant. The participant will sign the consent form, indicating they provide informed consent for participation. The form will be stored in a locked file cabinet separate from other information pertaining to the subject's participation. The participant will be given a copy of the consent form to take with them.

- vi) Describe potential risks, including physical, psychological, social, economic, or legal, as well as those that might arise due to a breach of confidentiality.  
(1) Identify their seriousness and likelihood.

The risks in this study involve procedures performed solely for the purposes of research. These risks include: psychological ratings, side-effects to the study medication, discomfort from interviewing, and unanticipated risks.

**Psychological Ratings:** Patients may find the battery of psychiatric and psychological tests tedious and boring, or intrusive. To aid the former, brief breaks will be given during assessment as needed. The latter concern is addressed through use of trained interviewers who have experience discussing sensitive material with clinical research subjects. It will be emphasized that participants can choose not to answer any question.

**Medication:** The most common side effects of naltrexone reported for the FDA-approved dosage used in this study are gastrointestinal discomfort, nausea, vomiting, headache, and fatigue (Anton, 2008) and a full list of side effects is listed in the consent form. Most side effects are mild and self-limiting and usually occur only during initial therapy. Naltrexone is relatively contraindicated in patients who have liver-enzyme levels that are four to five times above the upper limit of the normal range. Thus, blood tests of hepatic enzymes should be obtained about a month after the initiation of treatment. Such tests can be repeated monthly during a 4-month course of treatment (Anton, 2008). Participants will be told not to take any opiate medication while on naltrexone. Female participants will be instructed to practice consistent contraceptive use (or abstinence) and not to attempt to become pregnant. They will also keep a menstrual diary that will be reviewed with the physician. Participants will be monitored closely throughout the study via side effects check-ups and two medical screens after starting medication.

**Risks Pertaining to Loss of Confidentiality and Privacy:** Confidentiality of participants is a priority for research staff and also is presumed and must be maintained unless the investigator obtains the express permission of the subject to do otherwise. Risks from breach of confidentiality include invasion of privacy, as well as social and economic risks. Economic risks include alterations in relationships with others that are to the disadvantage of the subject, and may involve embarrassment, loss of respect of others, labeling with negative consequences, or diminishing the subject's opportunities and status in relation to others. There are some risks related to the use of cell-phones to collect daily data on drinking and medication adherence. Participants might receive texts while in the company of others and be questioned as to the nature of the message. If a participant leaves his/her phone unattended, it is possible that someone else could view an incoming text message. We will take steps to instruct participants to always keep the phone close by and recommend that the participant sets a password on the phone.

**Risks Pertaining to the Collection of Genetic Material:** The collection of genetic material entails additional potential risks of confidentiality. However, the collection of genetic material has become commonplace, and entails only minimal risk to study participants. The Genetic Information Nondiscrimination Act (GINA), which recently came into effect at the Federal level, protects individuals from discrimination from employers or insurance companies as a function of genetic risk markers. All participants will receive a statement summarizing GINA. All genetic material will be stored only with unique identifiers in the PI's laboratory. Participants will be informed in writing upon initial consent of the potential risks of genetic research. Consistent with our current protocols, the DNA sample will be kept for a period of 10 years at which time it will be destroyed. In the event that other single genetic markers (single nucleotide polymorphisms, or SNPs) are linked to response to naltrexone are identified, this will allow for analysis of those markers in the future. However, the planned analyses are presently limited to one genetic marker (OPRM1 A118G).

**Unanticipated risks:** Any study may involve risks that cannot be anticipated. Any identified risks will be reported immediately to UNMHSC HHRC for further consideration.

